Implementation plan for a physician-led clinical trial

Name of Clinical Trial:

Recognized Effects of Statin and Ezetimibe Therapy towards Reaching the LDL-C Goal

Scheduled period for the clinical trial: from July 1, 2009 to June 30, 2013

First edition created June 4, 2009

Revised edition October 17, 2012

Table of Contents

1. Background leading up to this study
2. Purpose and needs of the study
3. Brief overview of the study drugs
4. Study patients
5. Policy and procedure for explaining the study and obtaining consent
6. Trial methods
7. Endpoints
8. Observation and examination
9. Criteria for terminating treatment
10. Handling of adverse events
11. Reporting on deviations from the protocol
12. Termination, cessation, or suspension of the trial
13. Study period
14. Data collection and statistical analysis
15. Target number of cases and basis for setting it
16. Safety, human rights, and disadvantages faced by the study subjects
17. Cost burdens on the patients
18. Insurance coverage and compensation for health problems resulting from the study
19. Observance of the Declaration of Helsinki and GCP
20. Storage of records
21. Publication of research results
22. Background leading up to this study

With the ongoing westernization of many facets of Japanese lifestyle, diabetes and other lifestyle-related diseases have become a major problem for Japan. The diabetic population in Japan is increasing year by year. According to the 2006 National Health and Nutrition Survey conducted by the Ministry of Health, Labor and Welfare, 10.5 million Japanese people are confirmed diabetics and another 8.2 million are strongly suspected to have the disease. Hence, 18.7 million people are likely to be diagnosed with diabetes in the future, or 2.5 million more than were recorded a few years earlier in the survey of 2002 (an increase of 15.4%). With this increase in the diabetic population comes a higher incidence of diabetic microangiopathies and associated forms of ischemic heart disease and cerebrovascular disease. Improvements not only in glycemic control, but also in blood pressure and dyslipidemia, are recognized as important preconditions for good prognosis in these populations.

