Many reports have presented the inhibitory effects of statins on cardiovascular events. Yet according to the sixth annual interim report on the Japan Diabetes Complications Study (JDCS) published in 2004, the incidence rates of ischemic heart disease and cerebrovascular disease in diabetic populations were 6.7 / 1,000 humans per year and 6.5 / 1000 humans per year, or 3-4 times higher than the rates in the non-diabetic patients reported in the Hisayamacho study. Even now, the onset of cardiovascular events in patients with type 2 diabetes has become a major problem.

LDL cholesterol, a major risk factor for arteriosclerosis, comes from two sources: synthesis in the liver and absorption from the small intestine. Statins, the current first-line therapy for dyslipidemia, work mainly by inhibiting cholesterol synthesis in the liver. Statins have been reported to inhibit cardiovascular events and are confirmed to reduce various inflammatory markers in patients with type 2 diabetes. Recent progress in molecular biology has also made headway towards another clinical target, suppressing cholesterol absorption. Specifically, an inhibitor of the cholesterol transporter NPC1L1 expressed in the proximal portion of the small intestine has been found to inhibit cholesterol absorption in clinical studies. Ezetimibe, an agent that suppresses cholesterol absorption by binding to NPC1L1, has been accepted for clinical application in Japan since last year. According to clinical studies overseas, a combination of ezetimibe and statin is capable of conferring better control in the treatment of dyslipidemia compared to a stronger dose of statin.

Yet as of the present, there have yet to be appropriate reports in Japan on clinical results attained from the combination of the cholesterol absorption inhibitor ezetimibe with statins.

2. Purpose and needs of the study

1. Purpose

To evaluate the effect of combination therapy with ezetimibe and statin on type 2 diabetic subjects with hypercholesterolemia. The anti-inflammatory effects will be revealed by measuring inflammatory markers in both groups at the same time.

1. Needs of the study and clinical significance

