| Analysis sets fitting the protocol  Efficacy by PPS (Per Protocol Set) | Cases with the minimum compulsory program and available values for major variables, and without crucial contraventions of the protocol | Background, efficacy, safety |
| Analysis sets for safety | Prescribed cases with at a least single evaluation for safety | Background, safety |

(3) Statistical analysis

1) analysis for efficacy

The Wilcoxon rank sum test will be performed to analyze the percentage change in the level of serum LDL-C from baseline to week 12 of treatment.

The percentage of patients who reach the treatment goals at the end of the administration period will be calculated.

Wilcoxon signed rank test will be performed to analyze the change of examination data within each group.

2) The number and frequency of adverse effects will be calculated for subjects who receive at least a single administration of the study drugs. The same counting approach will be used for side effects.

15. Target number of cases and basis for setting it

(1) Target number of cases

Number of participating institutions: 25 institutions

Target number of cases: 120 cases

(2) Basis for setting the target number of cases

The first statin dose is assumed to account for 11.7% of the LDL-C-lowering effect in the double-dose statin administration group and 21.7% of the LDL-C-lowering effect in the ezetimibe add-on group. The SD is assumed to be 15 %, with an α of 0.05 and power of 90 %. Hence, there will be 60 cases per treatment group, assuming a dropout rate of 20 %.

16. Safety, human rights, and disadvantages faced by the study subjects

(1) Steps taken to protect human rights (Protection of privacy)

The confidentiality of the subjects must be duly considered when handling raw data for the study implementation, the consent form, etc. When case reports are to be submitted out-of-hospital, they will be handled using subject identification codes or the like. When the results of tests are published, the information will be screened to ensure that it cannot be used to identify the subjects. It will also be assumed, from the outset, that data on the subjects will not be used for any purposes other than the study.

17. Cost burdens on the patients

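### The only test named for the other lipids and hs-CRP is within each arm, so the plan states no between-arm analysis for its secondary endpoints

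*Protocol*

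**What the plan says.** The protocol describes a multicentre, open, active-control, parallel-group trial with allocation by minimisation (section 6, trial design). One strategy doubles the statin dose and the other adds ezetimibe. The title is "Recognized Effects of Statin and Ezetimibe Therapy towards Reaching the LDL-C Goal", and the purpose in section 2 includes this: "The anti-inflammatory effects will be revealed by measuring inflammatory markers in both groups at the same time".

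Section 7 makes LDL-C percentage change the primary endpoint. The first secondary endpoint is the proportion reaching the LDL-C goal. The second is percentage change in serum lipids and inflammation markers.

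Section 14(3) then names three efficacy analyses:

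- LDL-C percentage change to week 12: Wilcoxon rank sum test, which compares the arms.
- Goal attainment: "The percentage of patients who reach the treatment goals at the end of the administration period will be calculated".
- Other measurements: "Wilcoxon signed rank test will be performed to analyze the change of examination data within each group".

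The protocol states no between-arm analysis of any secondary endpoint.

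**The concern.** The trial allocates patients to two strategies so that they can be compared. Both strategies step treatment up, so a fall from baseline is plausible in both arms and does not isolate the contribution of ezetimibe. A signed rank test inside one arm asks whether that arm changed. It does not ask whether the arms changed by different amounts.

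The protocol is not merely silent here. It names a two-sample test for LDL-C and, in the same short list, a one-sample test as the only test for the data behind the second secondary endpoint. At stake is whether the results on hs-CRP and the other lipids come with any valid statement about combination therapy against a doubled statin dose. Goal attainment, the subject of the title, has a similar but weaker gap: no effect measure or interval is stated.

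**Working it through.** **1. The plan's own figure.** Section 15(2) assumes "11.7% of the LDL-C-lowering effect in the double-dose statin administration group and 21.7% of the LDL-C-lowering effect in the ezetimibe add-on group", a difference of 21.7 − 11.7 = 10 points. It also gives "The SD is assumed to be 15" (percent) and "with an α of 0.05 and power of 90" (percent). With a two-sided test:

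n per arm = 2 × (1.960 + 1.282)² × 15² / 10² = 47.3, rounded up to 48.

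Allowing for 20% dropout, 48 / 0.8 = 60 per arm and 120 in total. This matches "there will be 60 cases per treatment group, assuming a dropout rate of 20" (percent), so the sample size is not in question. It also shows that only LDL-C was sized, and gives 48 evaluable patients per arm for the checks below.

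**2. Endpoints against named analyses.**

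| Endpoint (section 7) | Analysis named (section 14(3)) | Compares arms? |
| --- | --- | --- |
| Primary: LDL-C % change | Wilcoxon rank sum | Yes |
| First secondary: goal attainment | Percentage calculated | Not stated |
| Second secondary: % change in lipids, inflammation markers | Wilcoxon signed rank in each group | No |

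**3. How within-arm tests behave when the arms do not differ.** Suppose both arms have the same true standardised change d, with 48 patients each. Let p be the chance that one arm's two-sided 5% test is significant (one-sample t power, used as an approximation to the signed rank test). The arms are independent, so the chance that exactly one is significant is 2p(1 − p). The values of d are assumptions; the protocol gives none for these markers.

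| d (SD) | p | 2p(1 − p) |
| --- | --- | --- |
| 0 | 0.050 | 9.5% |
| 0.1 | 0.104 | 19% |
| 0.2 | 0.274 | 40% |
| 0.3 | 0.530 | 50% |
| 0.4 | 0.775 | 35% |
| 0.5 | 0.924 | 14% |
| 0.6 | 0.983 | 3% |

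The 50% at 0.3 SD is the maximum that 2p(1 − p) can take, so the whole range should be read and not that row alone.

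Low discordance at large changes does not rescue the method. The protocol's LDL-C assumption for the doubled-statin arm is 11.7 / 15 = 0.78 SD, where discordance is about 0.1% because each arm is almost certain to be significant. The add-on arm, at 21.7 / 15 = 1.45 SD, would be significant as well. Two significant within-arm results would say nothing about the 10-point difference between them.

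**4. Regression to the mean, a conditional point.** Entry requires LDL-C of at least 120 mg/dL, or at least 100 mg/dL with CAD (section 4). The protocol does not say whether the qualifying value is also the baseline value. Simulation with no treatment effect used assumed values: on-statin mean 110 to 120 mg/dL, between-patient SD 22, within-patient SD 9 to 12, entry at 120, n = 48.

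- Qualifying value used as baseline: mean change about −1.8% to −4.3%; signed rank p < 0.05 in roughly 30% to 70% of arms.
- Separate baseline sample: rejection in about 5% of arms, the nominal rate.

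This was simulated for LDL-C. Lipids correlated with it would be affected to a lesser, unquantified degree. It need not apply to hs-CRP, on which patients are not selected.

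**5. What a between-arm analysis would deliver at 48 per arm.**

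- Goal attainment, 95% CI half-width with rates near 50%: 1.96 × √(2 × 0.25 / 48) = 0.20, or ±20 points. For assumed control rates of 30% to 60%, 80% power needs a difference of about 25 to 28 points.
- A continuous marker, 80% power: (1.960 + 0.842) × √(2 / 48) = 0.57 SD.

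**The case against.** The strongest reply is that this is detail for a statistical analysis plan. Only the protocol is at hand, it never says the signed rank test is the sole analysis of secondary endpoints, and the sentence also covers glucose and biochemistry, so it may be meant as a supplementary before-after summary. For goal attainment this largely stands. Percentages from two allocated arms can be set side by side, and a separate plan could add an interval or test. That part is an omission, not a wrong statement. For the second secondary endpoint the reply is weaker, because the protocol does choose a test and that test does not compare the arms.

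A reader might infer that the trial will claim an ezetimibe effect whenever one arm is significant and the other is not. The document does not say so, and where it clearly wants a comparison it names a two-sample test. The discordance table shows what that inference would cost if someone made it; it does not show an intention. Likewise, the inflammation aim implies a comparison through the design and the reference to both groups, but it is not framed as a formal between-arm hypothesis.

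A reader might also infer that regression to the mean will be credited to the drugs. That depends on an unstated baseline rule. The schedule in section 8 places consent at an observation stage and lipids at the initial visit, which leaves room for a separate baseline sample. The simulated marker, LDL-C, already has a between-arm primary analysis.

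**Conclusion.** The point holds at moderate severity and for the secondary endpoints only. As written, section 14(3) gives no between-arm inference for the other lipids and hs-CRP, and no effect measure or interval for goal attainment. Conclusions about differences drawn from paired within-arm tests would not carry a 5% error rate: with equal true changes, the arms disagree in about 3% to 50% of trials over 0 to 0.6 SD. That range rests on assumed effect sizes, 48 evaluable patients per arm and a t approximation.

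It would be too strong to say that the trial cannot answer its comparative questions. The data to be collected permit a valid comparison at analysis, and nothing in the protocol forbids one. The primary endpoint, its test and the sample size are unaffected. The regression-to-the-mean argument is secondary and applies only if the qualifying LDL-C is also the baseline.

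**What to change.** In section 14(3):

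- Make the week-12 analysis of the second secondary endpoint a between-arm comparison. Either the rank sum test already used for LDL-C or a baseline-adjusted difference with 95% CI would serve; if the latter, use the log scale for skewed markers such as hs-CRP and triglycerides. The choice between them is a modelling preference.
- Report goal attainment as a between-arm difference in proportions with 95% CI.
- Keep the signed rank results, described as within-arm summaries.
- Label the secondary results as supportive, because only LDL-C was sized. This also limits the weight placed on several additional comparisons.

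The cost is a wording change and a few more outputs, with no new patients, visits or measurements. The downside is visible imprecision: about ±20 percentage points for goal attainment at 48 per arm, and a marker difference of about 0.57 SD before power reaches 80%.

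### The stated 90% power is a normal-theory figure; the unadjusted Wilcoxon test named for the primary endpoint has about 88 to 89% under the same assumptions if the data are normal

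*Protocol*

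**What the plan says.** Protocol section 7(1) makes percentage change in serum LDL-C from baseline the primary endpoint. Section 14(3) assigns its test: "The Wilcoxon rank sum test will be performed to analyze the percentage change in the level of serum LDL-C". No covariate is named.

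Section 15(2) gives the planning values: "11.7% of the LDL-C-lowering effect in the double-dose statin administration group" and "21.7% of the LDL-C-lowering effect in the ezetimibe add-on group", then "The SD is assumed to be 15 %, with an α of 0.05 and power of 90" per cent. It concludes: "Hence, there will be 60 cases per treatment group, assuming a dropout rate of 20" per cent. Section 15(1) gives the total: "Target number of cases: 120 cases".

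Section 15(2) does not say which test the calculation was for, whether alpha is one- or two-sided, or what distribution is assumed. Section 14(2) lists a full analysis set and a per-protocol set for efficacy and does not say which is primary.

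**The concern.** The power in section 15 should describe the test in section 14. Here the size follows from a formula for comparing two means, while the comparison will be made on ranks. When data are normal with equal spread, the rank sum test is slightly less efficient than the comparison of means (asymptotic relative efficiency 3/π, about 0.955). The evaluable number that gives 90% for one test then gives a little less for the other.

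What is at stake is modest. A reader cannot match the stated power to the stated analysis. The plan also leaves unused a baseline LDL-C value that section 8 makes compulsory and that could sharpen the primary comparison without more patients.

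**Working it through.** **Inputs (Protocol section 15).** The two reductions are read as mean percentage changes, so the difference is 21.7 − 11.7 = 10 points. SD is 15 points, alpha 0.05, power 90%, dropout 20%, with 60 per arm and 120 in total.

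**Step 1: reproduce the plan's figure.** Two-sided normal approximation:

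n = 2 × (1.960 + 1.282)² × (15/10)² = 47.3, rounded up to 48 evaluable per arm.

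48 / 0.8 = 60 per arm, 120 in total. This matches exactly. A one-sided alpha of 0.05 gives 39 evaluable per arm and does not match, so the calculation was two-sided.

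**Step 2: normal-theory power at 48 per arm.** The standardised difference is 10 / (15 × √(2/48)) = 3.266.

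- z test: Φ(3.266 − 1.960) = 90.4%
- t-test (noncentral t): 89.8%

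**Step 3: Wilcoxon power at 48 per arm, normal data, same difference and SD.**

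- Efficiency approximation, effective n = 48 × 3/π = 45.8: 89.1%
- Simulation, 200,000 trials: 88.4% (repeat simulations ranged from 88.1% to 88.8%)

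The 200,000-trial simulation reaches 90% at 51 evaluable per arm; the efficiency approximation reaches it at 50.

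**Step 4: how far this depends on normality.** With difference 10, SD 15 and 48 per arm all held fixed, simulated power is:

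| Shape of percentage change | Wilcoxon | t-test |
|---|---|---|
| Normal | 88.1 to 88.8% | about 90% |
| t, 20 df | 89.4% | – |
| t, 10 df | 90.7 to 91.1% | 89.9% |
| Logistic | 91.6% | 89.7% |
| t, 5 df | about 94.5% | 89.8% |

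**Step 5: dependence on the number analysed.** If all 60 per arm contribute a week-12 value, Wilcoxon power under normality is 94.2%.

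**Step 6: adjusting for baseline.** If r is the correlation of the outcome with baseline LDL-C, the residual SD is 15 × √(1 − r²). The documents give no r, so the values below are assumptions. Power is from the noncentral t at 48 per arm.

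| Assumed r | Residual SD | Power |
|---|---|---|
| 0.1 | 14.92 | 90.1% |
| 0.3 | 14.31 | 92.3% |
| 0.4 | 13.75 | 94.1% |

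**The case against.** The strongest reply is that no stated figure is wrong. Section 15(2) names no test, its size follows from its own inputs, and planning with a normal formula for a trial analysed by ranks is a common approximation. All of this stands.

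The shortfall also needs normality, which the Protocol does not assume. A difference of 10 and an SD of 15 do not by themselves make the Wilcoxon test weaker, and step 4 shows the sign reversing with modestly heavier tails. This stands too, and it rules out a flat statement that the planned test delivers 88%.

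The gap is smaller than the uncertainty in the planning SD. Under normality an SD of 14.6 restores 90% for the Wilcoxon test, and an SD of 15.5 lowers it to about 86%.

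The 94% with all 60 per arm carries less weight. The full analysis set does keep treated cases, but section 15(2) itself allows for 20% dropout, and the Protocol states no way to supply a missing week-12 LDL-C. On the Protocol's own planning terms, 48 is the number to use.

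Finally, the gain from ANCOVA rests on correlations that the document does not give. At r = 0.1 nearly all of the improvement comes from leaving ranks for a normal-theory test, and that holds only while residuals are roughly normal.

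A reader might infer that the trial is undersized and should recruit 126 to 128 patients (50/0.8 = 62.5, so 63 per arm; 51/0.8 = 63.75, so 64 per arm). The documents do not support that: the figure holds only under exact normality, and the difference lies within the uncertainty of the planning assumptions.

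**Conclusion.** The mismatch is real and small. Section 15(2) reaches 60 per arm by a two-sided normal-theory comparison of means, while section 14(3) specifies an unadjusted rank test. Under normality, with SD 15, difference 10 and 48 evaluable per arm, that test has about 88 to 89% power, 1 to 2 points below the stated 90%. The target of 120 is arithmetically correct, and nothing here shows that the trial cannot answer its question.

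The point is worth making for two reasons: the stated power cannot be matched to the named analysis, and an adjusted primary analysis using data already collected is available at almost no cost.

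**What to change.** Keep 120 patients. In section 14(3), before outcome data are seen, make the primary comparison of percentage change in LDL-C an ANCOVA with treatment group, baseline LDL-C and entry statin (atorvastatin or pitavastatin), and retain the Wilcoxon rank sum test as sensitivity analysis. Both covariates are known before allocation: section 8 requires baseline LDL-C, and the entry criteria in section 4 fix the statin.

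The cost is one or two sentences and no extra patients or measurements. The downside is reliance on roughly normal residuals, which the Wilcoxon analysis helps to check. With heavy tails and a weak baseline correlation, the rank test could be the more powerful of the two.

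If the Wilcoxon test stays primary, change section 15(2) only. Say that 60 per arm comes from a two-sided normal-theory comparison of means, and that Wilcoxon power with 48 evaluable per arm is about 88 to 89% if percentage changes are normal with SD 15. The condition should be stated with the figure. This costs one sentence and a slightly less favourable number.
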